## Abstract

**Background:**

Sickness absence due to common mental disorders (such as depression, anxiety disorder, adjustment disorder) is a problem in many Western countries. Long-term sickness absence leads to substantial societal and financial costs. In workers with common mental disorders, sickness absence costs are much higher than medical costs. In the Netherlands, a practice guideline was developed that promotes an activating approach of the occupational physician to establish faster return-to-work by enhancing the problem-solving capacity of workers, especially in relation to their work environment. Studies on this guideline indicate a promising association between guideline adherence and a shortened sick leave duration, but also minimal adherence to the guideline by occupational physicians. Therefore, this study evaluates the effect of guideline-based care on the full return-to-work of workers who are sick listed due to common mental disorders.

**Methods/design:**

This is a two-armed cluster-randomised controlled trial with randomisation at the occupational physician level. During one year, occupational physicians in the intervention group receive innovative training to improve their guideline-based care whereas occupational physicians in the control group provide care as usual. A total of 232 workers, sick listed due to common mental disorders and counselled by participating occupational physicians, will be included. Data are collected via the registration system of the occupational health service, and by questionnaires at baseline and at 3, 6 and 12 months. The primary outcome is time to full return-to-work. Secondary outcomes are partial return-to-work, total number of sick leave days, symptoms, and workability. Personal and work characteristics are the prognostic measures. Additional measures are coping, self-efficacy, remoralization, personal experiences, satisfaction with consultations with the occupational physician and with contact with the supervisor, experiences and behaviour of the supervisor, and the extent of guideline adherence.

**Discussion:**

If the results show that guideline-based care in fact leads to faster and sustainable return-to-work, this study will contribute to lowering personal, societal and financial costs.

**Trial registration:**

ISRCTN86605310

## Background

Sickness absence due to common mental disorders (CMD), such as depression, anxiety disorder and adjustment disorder, is a problem in many Western countries, including Sweden, Germany, the UK and the Netherlands [1]. Moreover, CMD have negative consequences for the worker. They affect functioning in private life and can lead to long-term absenteeism, which is associated with individual suffering, reduced probability of eventual return-to-work (RTW), a weakened financial position, social isolation, and exclusion from the labour market [2,3]. Only 50% of the workers sick listed for 6 months or more return to their work [4]. In workers with CMD, sickness absence costs are reported to be much higher than the medical costs, mainly due to the long duration of a sick leave period [5,6]. In addition, (long-term) sickness absence leads to substantial social and financial costs for society [3]. In the Netherlands, about one third of people receiving disability benefits do so because of mental health problems [7,8] of which most are CMD [7]. The annual costs of sickness absence due to CMD are estimated at 2.7–7.5 billion euros [6,9].

In 2000, the Netherlands Society of Occupational Medicine (NVAB) developed a practice guideline entitled ‘The management of mental health problems of workers by occupational physicians’ and revised it in 2007 [10,11]. This guideline, which is both practice and evidence-based, promotes an activating approach by the occupational physician (OP) aimed to establish faster RTW by enhancing the problem-solving capacity of workers, especially in relation to their work environment [7]. The guideline was disseminated among Dutch occupational health services (OHS) and OPs. In addition, educational meetings were organised (nationally and locally) for OPs to increase their knowledge on the guideline content. The OPs themselves and the OHS are expected to obtain the required skills to perform in accordance with the guideline. However, a retrospective study showed that the quality of the occupational care provided did not fully meet the requirements of the guideline, and that in workers with adjustment disorders closer adherence to this guideline was associated with a shortened sick leave duration [12]. Another Dutch study provided OPs with a three-day training in guideline use; results showed that, although their compliance was minimal, OPs had a positive attitude towards using the guideline [6,13]. Therefore, present study investigates whether guideline adherence leads to faster and sustainable RTW of workers with CMD.

### Aim of this study

To evaluate the effect of guideline-based care by OPs on the full RTW of workers sick listed due to CMD.

## Methods/design

In describing the design of this study the CONSORT 2010 statement was followed to improve the reporting quality for randomized controlled trials (RCT) [14].

### Study design

The study is designed as a two-armed cluster RCT with randomisation at the OP level (Figure 1). All participating OPs are recruited from a large collaborating OHS in the Netherlands. The OPs are randomised to an intervention group or a control group. Using an innovative training, OPs in the intervention group are trained to counsel sick-listed workers according to the Dutch national guideline ‘Management of mental health problems of workers by occupational physicians’. OPs in the control group receive no training and counsel sick-listed workers with care as usual. Workers are invited by the OHS after their first meeting with the OP. Data on sick leave and RTW of all invited workers are anonymously extracted from the registration system of the OHS during 1-year follow-up. In addition, in case of consent the worker receives a questionnaire at baseline (T0), and at 3 months (T1), 6 months (T2) and 12 months (T3) post baseline. In addition, 2 months after baseline a short questionnaire is sent to their supervisor.

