### Recruitment of participants

The study is conducted in the southern part of the Netherlands. The workers eligible for this study are on sick leave due to CMD diagnosed by the OP, counselled by an OP participating in the study, have had a first meeting with the OP, and are aged 18–65 years. From all eligible workers data on sick leave and RTW will be extracted from the registration system of the OHS anonymously.

Workers eligible for the data collection by means of the questionnaires work at one of the ± 320 companies served by this collaborating OHS that gave permission to invite their workers. The companies vary in size and serve different sectors. These workers are selected from the registration system of the OHS after their first consultation with the OP. They are sent an invitation letter from the OHS, as well as written information about the study. Workers who do not want to be contacted further can indicate this on a reply card. All eligible participants are contacted for additional information, and to check the inclusion and exclusion criteria. If the worker is willing to participate in the study and meets all the selection criteria, an informed consent and the baseline questionnaire will be sent to the worker.

Inclusion criteria for this study are: 1) CMD is the primary reason for sick leave diagnosed by an OP according to the Dutch Classification of Diseases (CAS) which is based on the ICD-10, 2) on current sick leave when selected from the registration system of the OHS after the first meeting with the OP, and 3) adequate command of the Dutch language. Exclusion criteria are: being suicidal, and a physical problem being the primary reason for sick leave at the time of study inclusion.

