#### Prognostic measures

•Personal characteristics such as age, gender, level of education, sick leave in the previous year, history of mental disorders, and expectations about full RTW are measured at baseline.

•Work characteristics such as number of working hours, contract type, type of work, profession and job content are measured at baseline. Job content is measured with the Dutch version of the Job Content Questionnaire (JCQ) [25], a self-report questionnaire which measures the social and psychological characteristics of jobs. The JCQ assesses the following scales: psychological job demands, decision latitude, social support, physical demands and job insecurity.

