### Statistical analysis

Survival analyses will be used to analyse the primary outcome (time to full RTW) and the time to partial RTW comparing the intervention and the control group, while taking into account the effect of clustering of workers within OPs. Longitudinal multilevel analysis will be used to analyse the secondary outcomes.

To detect significant differences in the baseline characteristics between the intervention group and control group descriptive analyses will be used. If necessary these differences will be taken into account in the effect evaluation.

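### The registry extract that carries the primary outcome is described as anonymous sick leave and RTW data only, so the planned adjustment for baseline differences is not secured in that population

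*Protocol article*

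**What the plan says.** **Source of the primary outcome.** Table 1 gives the registration system of the occupational health service as the only source of full RTW. The article describes the extract twice.

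- Study design: "Data on sick leave and RTW of all invited workers are anonymously extracted from the registration system of the OHS during 1-year follow-up".
- Recruitment of participants: "From all eligible workers data on sick leave and RTW will be extracted from the registration system of the OHS anonymously".

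**Source of the baseline data.** Questionnaire recruitment is narrower: "Workers eligible for the data collection by means of the questionnaires work at one of the ± 320 companies" that allowed their workers to be approached. Those workers are then contacted: "All eligible participants are contacted for additional information, and to check the inclusion and exclusion criteria". Under Study design, "in case of consent the worker receives a questionnaire at baseline (T0", with follow-up questionnaires after that. Under Prognostic measures, personal characteristics including "sick leave in the previous year, history of mental disorders, and expectations about full RTW are measured at baseline", as are work characteristics and job content. Table 1 marks them at T0 and names no registry source for any of them.

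**Use of the baseline data.** The Statistical analysis section plans a survival analysis that allows for clustering by OP. It then looks for significant baseline differences between the groups and adds: "If necessary these differences will be taken into account in the effect evaluation". It names neither the covariates nor the population.

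**The concern.** The outcome and the covariates are described for different sets of workers. The outcome is extracted for everyone eligible (or everyone invited) and is said to be anonymous and to consist of sick leave and RTW data. The covariates exist for consenting workers. An analyst who follows the text has two options:

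- analyse all registry workers without covariates; or
- adjust, and thereby restrict the primary analysis to consenters whose two records can be matched.

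The second option matters in a cluster trial. OPs are randomised first, and workers are invited only after their first meeting with an OP who is already allocated. Consent is therefore a post-randomisation event. Confining the primary analysis to consenters in order to gain covariates gives up the main advantage of the registry data, which is that they do not depend on who agrees to take part. Because adjustment is triggered by what the baseline comparison shows, the choice of population could also end up being made after the data are seen.

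**Working it through.** **1. Three nested populations.** Setting the sections side by side:

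| Set | Where defined | Registry outcome | T0 questionnaire |
|---|---|---|---|
| All eligible workers | Recruitment of participants | yes, anonymous | no, unless invited and consenting |
| All invited workers (companies that gave permission) | Study design; Recruitment of participants | yes, anonymous | no, unless consenting |
| Included, consenting workers | Study design; Sample size (232) | yes, as part of the sets above; linkage not stated | yes |

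Invited workers are a subset of eligible workers, and consenters a subset of the invited. No section says which set carries the primary analysis. The Sample size section points both ways. It speaks of 232 workers to be included, and the Discussion treats reaching that number as a recruitment task. Yet the 5% attrition allowance is placed on the sick leave data, which come from the registry and do not depend on questionnaire return.

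**2. The plan's own figure.** Inputs from the Sample size section: RTW 55% v 75% at 3 months and 75% v 90% at 6 months, power 80%, alpha 0.05 (taken as two-sided), ICC 0.025.

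n per arm = [1.960·√(2p̄(1−p̄)) + 0.842·√(p₁(1−p₁)+p₂(1−p₂))]² / (p₁−p₂)²

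- 3 months: p̄ = 0.65, n = 88.1, rounded up to 89.
- 6 months: p̄ = 0.825, n = 99.5, rounded up to 100.

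Design effect = 1 + (m−1)×0.025, where m is the number of workers per OP. The Sample size section does not state m.

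- m = 5 gives 1.10: 88.1 × 1.10 = 96.9 → 97, and 99.5 × 1.10 = 109.5 → 110. Both match the plan.
- m = 232/60 = 3.87, from the Discussion, gives 1.072. Applied to the rounded 89 and 100 this is 95.4 → 96 and 107.2 → 108, slightly below the plan.

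Attrition: 220/0.95 = 231.6 → 232, as stated.

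The sample size therefore stands. Neither linkage nor covariates enter it, so this point changes no figure in it.

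**3. What adjustment needs, and what the text provides.**

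- *Clustering by OP.* The survival analysis needs an OP identifier on every record. The extract must therefore hold more than sick leave and RTW dates, although the article does not say so.
- *Selection of workers.* Eligibility uses age 18–65 and a mental disorder diagnosis under the Dutch classification (CAS), with workers selected from the registration system. Age and CAS code should therefore be available for every eligible worker.
- *Gender, contracted hours, previous-year absence.* The registry may hold these. That is an assumption.
- *RTW expectations and job content.* These are self-reported and do not exist for workers who do not consent.

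A usable covariate set is thus probably available for everyone, but the described extract does not include it and the described adjustment does not call for it.

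**The case against.** **The wording may be innocent.** The text calls the extract anonymous but never says that linkage is impossible. The ordinary meaning may be data without names. The health service selects and invites workers from this same system, participants sign consent, and Table 1 lists registry and questionnaire measures on one time path. An article may leave linkage keys to the full protocol. This stands. A reader might infer that registry records can never be joined to questionnaires, and the document does not support that. What remains is that the article fixes the extract as sick leave and RTW data and then plans an adjustment without saying where covariates for the registry population come from.

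**Anonymity is not the main cause.** For non-consenters the questionnaire data never exist, and a study code would not create them. This also stands, and it is why the remedy lies in registry-held covariates rather than in re-identification.

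**Adjustment is only conditional.** True, and the factors are not named. But a conditional plan still has to be feasible in the population to which it applies.

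**Eligibility.** A reader might infer that workers found ineligible on contact remain in the primary data. The criteria "Exclusion criteria are: being suicidal, and a physical problem being the primary reason for sick leave at the time of study inclusion" are checked by contact (mode not stated) on the questionnaire route. The article first defines registry eligibility without that check: sick leave for a common mental disorder, a participating OP, a first meeting, and age. The main diagnosis comes from the OP. The text therefore does not show that ineligible workers enter the registry set.

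**Additional measures.** Coping, self-efficacy and similar factors are to be reported apart from the trial results, so they place no demand on the primary analysis.

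**Conclusion.** The point holds as a gap between the described extract and the described adjustment. Read as written, baseline differences could be taken into account only among consenters recruited after OP randomisation, and only if their registry records can be linked. The article also leaves open whether all eligible workers, all invited workers or the 232 included workers carry the primary analysis.

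No numerical size can be given. The document states neither the consent rate, nor the number of eligible or invited workers, nor how strongly any covariate predicts RTW. A reader might want to turn the lost covariates into a loss of power. That would need an assumed explained variance, and a calculation on two proportions would not carry over directly to the planned survival model. The stated sample size is unaffected.

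The verdict assumes that the baseline characteristics come mainly from the T0 questionnaire, since the article does not give the source item by item. It also assumes that age and CAS code can be exported because they are used for selection.

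**What to change.** 1. **Widen the export.** For every eligible worker, export OP code, agency, age and CAS diagnosis with the sick leave and RTW dates. Add gender, contracted hours and previous-year absence if the registry holds them. No names and no re-identification key are needed.
2. **Pre-specify the adjustment.** Adjust the primary survival model for a named set of these variables in all workers, in place of adjustment triggered by significant baseline differences. Include agency, since the Randomisation section places allocation at agency level. The OP assigns the diagnosis after allocation, and diagnosis is part of the guideline being trained, so also report the model without it.
3. **Name the primary population.** Reconcile Study design, Recruitment of participants, Sample size and Statistical analysis on whether it is all eligible, all invited or the 232 included workers.
4. **Limit linkage to consenters.** Link questionnaires to registry records by study code for consenting workers only, and say so. Treat analyses that use questionnaire covariates as supplementary.

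**Cost.** A slightly wider registry export, a few sentences of text and possibly a note to the ethics committee. Self-reported factors such as RTW expectations would still be unavailable for non-consenters, which no change to the extract can remedy.

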**Figure 1 F1:**
[figure not shown]
Flow diagram of the study design.

The Medical Research Ethics Committee of Elisabeth Hospital in Tilburg approved the study design, protocol, information letter and brochure, questionnaires, and informed consent. Participation of workers is voluntary and all participants signed an informed consent. Each participant was informed about their right to withdraw from the study at any time.

### Intervention

#### Intervention/guideline-based care

The Dutch guideline ‘The management of mental health problems of workers by occupational physicians’ promotes an activating approach of the OP as case and care manager to enhance the problem-solving capacity of the workers to achieve RTW. The guideline is based on cognitive behavioural principles to enhance the problem-solving capacity of workers in relation to their work environment, and process-based evaluation.

The guideline consists of four consecutive steps:

1) Problem orientation and Diagnosis: an early involvement of the OP is promoted (first assessment and start of counselling about 2 weeks after the worker reported sick). A simplified classification of mental health problems is introduced in four categories: i) Stress-related complaints, ii) depression, iii) anxiety disorder, and iv) other psychiatric disorders. Furthermore, problem inventory should focus on factors related to the worker and their work environment and the interaction between these two.

2) Intervention/Treatment: the OP acts as case manager by monitoring and evaluating the process of recovery (process-based evaluation). When recovery stagnates OPs should intervene by acting as care manager by using cognitive behavioural techniques to enhance the problem-solving capacity of the worker, providing the worker and work environment with information/advice on the recovery and the RTW process, contact the general practitioner when problems remain the same or increase, and refer the worker to a specialised intervention when necessary. In addition, the OP should advise the work environment (e.g. supervisors, managers, human resource managers) how to support the worker and enhance the recovery and RTW process.

3) Relapse prevention: Integration of relapse prevention from the first contact with the worker by enhancing the problem-solving capacity of the worker.

4) Evaluation: During follow-up meetings evaluation of the recovery process includes the perspectives of the worker, supervisor, and other involved professionals. Follow-up meetings with the worker should take place every 3 weeks during the first 3 months, and then every 6 weeks thereafter. The supervisor or work environment should be contacted once a month. Follow-up contacts with the general practitioner or other professionals should take place when the recovery process stagnates or when there is doubt about the diagnosis or treatment.

#### Content of the training

OPs participating in the study and allocated to the intervention group received training in the guideline before the start of the study. This training was specifically designed for the purpose of this study and consisted of 8 meetings within 12 months. Each meeting took 2 h and was provided in groups of 4-6 OPs under the guidance of a trainer. The aim of the training was to enhance guideline adherence of the participating OPs by focussing on barriers that prevent OPs from using the guideline and finding solutions to overcome these barriers. This is considered to be a successful strategy for the implementation of guidelines [15,16].

During the 8 meetings the (key) recommendations within each consecutive step of the guideline were discussed. These discussions first focussed on barriers that would hinder OPs from using the specific recommendation in practice. The analysis of barriers was structured and based on an existing framework of barriers [17]. According to this framework guideline adherence can be affected by three main categories: 1) knowledge-related barriers (lack of awareness and lack of familiarity), 2) attitude-related barriers (lack of agreement, lack of self-efficacy, lack of outcome expectancy and lack of motivation/inertia of previous practice) and 3) external barriers that hinder physicians to apply the guideline in practice (guideline factors, environmental factors and patient factors). Second, the OPs in the group were invited to suggest solutions to address the perceived barriers taking into account the context of their daily practice. Third, the OPs drew up an action plan of how to implement these solutions in their daily practice, and agreed on learning objectives and ‘homework’ assignments. Between the meetings (a period of about 6 weeks) the OPs practiced the suggested solutions to experience if and how these would help to apply the guideline recommendations. During the next meeting the experiences of the OPs were evaluated and, when necessary, the solutions were adjusted to what the OPs had experienced in practice. This cycle of plan-do-check-act was repeated in each meeting for all the recommendations stated in the guideline.

